Control subjects will be enrolled for the purposes of assay development, including establishing the biomarker reference intervals, and will be cohorted into groups based on age and sex. These will include 120 trauma controls through 14 day follow up, and 120 healthy controls with a single visit. Trauma controls are defined as patients presenting to the ED for a traumatic injury and requiring an X-ray, but who do not have head trauma. Healthy controls will be subjects that report to be healthy and are not taking any prescription medications.

The BRAINBox TBI Test results determining a diagnosis of ATE, will be compared to the expert clinical diagnosis. Adjudicated patients assigned a diagnosis of TBI will be stratified for having high or low risk for post-concussive symptoms in each symptom category, based on biomarker and neuropsychiatric testing, and are defined as either “ATE with” or “ATE without” post-concussive symptoms. The high or low risk for post-concussive symptoms in each symptom category is defined using the validated interpretation guides for each test (Table 3), relevant literature with input from Key Opinion Leaders.

**Table 3 T3:** Symptom categories with corresponding neurocognitive and neuropsychological tests.

**Neuropsychological/ Neurocognitive Test**	**Symptom Category**
Headache Impact Test (HIT-6)	Headache
Dizziness Handicap Inventory, Convergence Insufficiency Symptom Survey, Balance Error Scoring System (BESS)	Motor Impairment (Balance, Dizziness/Vertigo, Visual Dysfunction)
Patient Recorded Outcome Measurement Information System (PROMIS), Sleep Disturbance Short Form	Sleep Disturbance
Glasgow Outcome Scale-Extended (GOSE-E), BrainCheck	Cognitive (Memory, Attention, Concentration, Executive Function)
Generalized Anxiety Disorder (GAD-7), Post-traumatic Stress Disorder Checklist for DSM-5 (PCL-5), Patient Health Questionairre-9 (PHQ-9), and Perceived Stress Scale	Psychological (Depression, Anxiety, Mood, Irritability, Post-traumatic Stress Disorder PTSD)

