The performance of a prognostic ATE test will be determined by evaluating the biomarker values, neurocognitive assessments, and baseline demographics at the index visit, as predictors of 3 separate models that assign high or low risk to a subject for subsequent symptom occurrence at 14, 30, and 90 days. Symptom categories and tests performed during the study are provided in Table 3. Symptoms are evaluated as a composite at each time point, with thresholds to stratify subjects defined based on the scoring system/scale for each assessment, identifying the subject's risk for a specific symptom category at each time point. A separate statistical/machine learning algorithm will be developed for each time point that calculates the risk at the specific time after injury. In the algorithm, the definition of high or low risk for having post-concussive symptoms is defined by the decision threshold that produces the minimum sensitivity and specificity of 85 and 75%, respectively. For the validation process, the finalized algorithms will be applied to the subject's biomarker values, NC assessments, and baseline demographics (age and sex) at the index visit. If the output of the algorithm exceeds the identified decision threshold, the subject will be classified as high risk. Otherwise, the subject will be classified as low risk for post-concussive symptoms at the specified time point. The prognostic report is designed to aid the clinician in determining the subject's risk of having post-injury post-concussive symptoms at 14, 30, and 90 days.

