### Statistical Analysis

#### Sample Size Estimation

Sensitivity and specificity are used to determine performance, since both are essential in the characterization of diagnostic effectiveness of the BRAINBox TBI Test.

The following assumptions were used to calculate sample size for the primary endpoint (within 96 h of injury) with the blood specimens collected at the first-time point: a one-sample binomial test, a clinical sensitivity of 0.85 and specificity of 0.75, a “difference to detect” of 0.07, alpha of 0.05 and a power of 0.80. The assumptions for sensitivity and specificity are based on findings from HeadSMART pilot trial (30).

The sample size is based on the binomial test for a one sample design using a two-sided significance level of α = 0.05 and a power of 1-β = 0.80 (30). The following hypothesis will be tested:

$$H_{01}:Se=Se_{0}and\;H_{02}:Sp=Sp_{0}(null\;hypotheses)$$

$$H_{\text{a1}}:Se\neq Se_{0}\;and\;H_{\text{a2}}:Sp\neq Sp_{0}(alternative\;hypothesis)$$

Where *Se* (sensitivity) is the proportion of target condition positive subjects that yield a positive test result, *Sp* (specificity) is the proportion of target condition absent subjects that yield a negative test result, Se_0_ is the desired sensitivity and Sp_0_ is the desired specificity.

Generically for both sensitivity and specificity, let p_0_ represent the null value, p_1_ the alternative and let *n* and *m* represent the sample size and the number of observed outcomes of interest, respectively. Based on the binomial distribution, the sample size may be calculated using a numerical approach by solving two equations simultaneously. For a given two-sided significance level α (Type I error), there exists a critical value *c* (nonnegative integer), such that:

$$\sum_{i=c}^{n}\left(\begin{array}{c} n\\ i \end{array}\right)p_{0}^{i}{\left(1-p_{0}\right)}^{n-i}\leq 1-\alpha /2$$

and

$$\sum_{i=c}^{n}\left(\begin{array}{c} n\\ i \end{array}\right)p_{1}^{i}{\left(1-p_{1}\right)}^{n-i}\leq 1-\beta$$

If m ≥ c, then the null hypothesis is rejected at α significance level. There exists the smallest sample size *N*, such that as long as *n* ≥ N, the power is always greater than or equal to 1-β. Then, *N* is the sample size from exact binomial testing.

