### Prognosis of ATE

A separate model will be fit for symptoms at each post-enrollment time point, with data evaluated during the modeling phase, to determine the prognostic output report. Results will be grouped into low and high risk. Based on the data from the modeling/training phase, the symptom categories that are statistically supported, with sufficient prevalence to make a justified prognostic claim, will be reported. If applicable, symptoms categories may be combined into one overarching composite result, and defined as either low or high risk. Data handling for modeling will be the same as the diagnostic analysis, with the models identifying the likelihood that a subject will experience ATE symptoms at 14, 30, and 90 days.

Sample size for TBI subjects adjudicated as high or low risk for ATE symptoms at 14, 30 and 90-days post-injury is based on estimated prevalence of 60% of subjects having unresolved or emergent injury-related symptoms in the suspected ATE population at each time point (30). Using published and internal information on prevalence, as well as predefined sensitivity, specificity, confidence intervals, error, the total number of ATE subjects needed was calculated. The number of subjects with high risk of outcomes needed, the target condition for the prognosis, will be 236 evaluable subjects. The number of subjects without ATE will be 157, yielding a total number of subjects of 393 for algorithm training. With the estimated prevalence of ATE being 50%, a total of 786 blunt head trauma subjects is needed for algorithm training. This study design uses the same sample sizes for both training and validation phases, just as in the diagnostic models. Therefore, the same number of blunt head trauma subjects (*n* = 786) are needed for validation. To provide sufficient data for prognosis modeling in training and validation cohorts, up to 1,600 suspected ATE subjects will be needed. Enrollment numbers are subject to increase or decrease pending on true prevalence, results of data analysis and/or attrition.

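### The prognostic reference outcome is defined inconsistently: one statement builds it partly from biomarkers that are also predictors, and the negative group is mislabelled

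*Protocol article*

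**What the plan says.** Predicting persistent symptoms up to 90 days is one of the article's two primary objectives. Its reference outcome is described in several places.

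- **Methods, paragraph on enrolment and adjudication (after Table 2).** Prognosis is confined to subjects adjudicated TBI-positive, who are then classified by whether symptoms are present at each time point.
- **Methods, paragraph just before Table 3.** Adjudicated TBI patients are "stratified for having high or low risk for post-concussive symptoms in each symptom category, based on biomarker and neuropsychiatric testing"; on that basis they are defined as ATE with or ATE without post-concussive symptoms. The next sentence says the risk classes come from the interpretation guides of the Table 3 tests, plus literature and expert input. Table 3 lists no biomarker.
- **Algorithm Training and Testing, prognostic paragraph.** Index-visit biomarkers, neurocognitive assessments and demographics are the predictors. Symptom thresholds come from each assessment's scale. The sentence that sets the algorithm's cut-off reads: "the definition of high or low risk for having post-concussive symptoms is defined by the decision threshold that produces the minimum sensitivity and specificity". The minima are 85% for sensitivity and 75% for specificity.
- **Prognosis of ATE.** The sample size concerns TBI subjects adjudicated as high or low risk, and high risk is called the target condition, with 236 subjects. Of the remainder it says "The number of subjects without ATE will be 157", for a total of 393. The symptom rate is an "estimated prevalence of 60% of subjects having unresolved or emergent injury-related symptoms in the suspected ATE population at each time point". A 50% ATE prevalence then gives 786 blunt head trauma subjects per phase.

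**The concern.** A prognostic accuracy study needs a reference outcome determined independently of the test. If biomarker results help decide who counts as having post-concussive symptoms, an algorithm using those biomarkers will agree with the outcome partly by construction. That is incorporation bias, and it pushes apparent sensitivity, specificity and AUC upwards. A validation cohort does not remove it, because the same contaminated outcome is applied there.

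The labelling makes the wrong reading easier. When the truth and the prediction are both called high or low risk, the two margins of the accuracy table share a name. Calling the negatives subjects without ATE invites an analyst to take them from the TBI-negative group. Prognostic specificity would then partly re-measure diagnosis.

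**Working it through.** **1. The outcome definitions side by side**

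| Place in the article | What sorts subjects | Biomarkers used? |
|---|---|---|
| Methods, enrolment and adjudication paragraph | Presence of symptoms at each time point | No |
| Methods, sentence before Table 3 | Biomarker and neuropsychiatric testing | Yes |
| Methods, next sentence, with Table 3 | Interpretation guides of the listed tests, literature, expert input | No |
| Algorithm Training and Testing | Scale thresholds of each assessment | No |

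Three statements give a symptom-based outcome without biomarkers. One does not, and it is the one that names the outcome groups. Because the predictors include index-visit biomarkers, that statement taken literally puts predictors into the reference.

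**2. Two uses of one label**

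High/low risk is the reference class in Methods before Table 3. In Prognosis of ATE it is the target condition and an adjudicated status. In Algorithm Training and Testing it is the algorithm's output.

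**3. Reproducing the sample size**

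Inputs from Sample Size Estimation: "a clinical sensitivity of 0.85 and specificity of 0.75"; a difference to detect "of 0.07, alpha of 0.05 and a power of 0.80"; an exact one-sample binomial test, two-sided. The direction of the difference is not stated. The figure is reproduced with a null of 0.85 and an alternative of 0.78.

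- For each n, take the largest c with P(X ≤ c | n, 0.85) ≤ 0.025. Power is P(X ≤ c | n, 0.78).
- The smallest n with power of at least 0.80 is 236 (power 0.802).
- 236 / 0.60 = 393.3, so 393.
- 393 × 0.40 = 157.2, so 157; and 236 + 157 = 393.
- 393 / 0.50 = 786.

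All four figures are recovered. (The article's further condition that power stay at or above 80% for every larger n would give 255 instead of 236; that does not bear on this point.)

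**4. Who the 157 are**

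Dividing by the 50% ATE prevalence converts a number of ATE subjects into a number of blunt head trauma subjects, so all 393 must have ATE. The 157 are the 40% of ATE subjects without symptoms. If they were subjects without ATE, 393 would mix two populations and 393 / 0.50 would have no meaning. The 236 alone would need 236 / 0.50 = 472 blunt head trauma subjects if every ATE subject had symptoms, or 236 / (0.60 × 0.50) = 787 at a 60% rate.

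**5. The population for the 60%**

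Let x be the symptom rate among ATE subjects and y the rate among suspected subjects without ATE. If 60% is the rate in all suspected subjects, as written, then 0.60 = 0.5x + 0.5y, so x = 1.2 − y. With y between 0 and 1, x lies between 0.2 and 1.0. The ends are algebraic limits, not plausible values. The article gives no y, so the values of x below are assumptions.

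| Assumed x | Split of 393 ATE subjects (with / without symptoms) | Blunt head trauma subjects needed for 236 with symptoms, 236 / (0.5x) |
|---|---|---|
| 0.4 | 157 / 236 | 1,180 |
| 0.6 (as used) | 236 / 157 | 787 (the article rounds to 393 first: 786) |
| 0.8 | 314 / 79 | 590 |

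The 236/157 split therefore follows only if 60% is the rate within adjudicated ATE.

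**The case against.** The strongest reply is that this is loose drafting and not the plan. Three of four statements give a biomarker-free outcome, one of them directly after the problem sentence. That sentence may simply merge a description of what the test does with the names of the outcome groups. The adjudicators are blinded to the test results when they diagnose TBI, and the article refers to a blinding plan that is not shown. This reply stands in part: circularity is not established as the intended analysis. But the sentence says how the groups are defined, and a reader of the article cannot tell which definition governs a primary objective.

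Four stronger readings are tempting and should not be drawn.

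- **That the outcome is defined by the model's own cut-off.** The sentence in Algorithm Training and Testing is limited to the algorithm. A cut-off chosen to reach a given sensitivity and specificity presupposes a separate reference, and the same paragraph supplies one through scale thresholds. The fault is the shared label.
- **That the sample size has a wrong denominator.** It does not; the arithmetic closes with ATE subjects throughout. No section plans an analysis with TBI-negative subjects as prognostic negatives.
- **That the inflation can be quantified.** The article gives no weight for biomarkers in any outcome, so any simulated AUC would reflect invented weights.
- **That BrainCheck is circular because it is both a predictor and a Table 3 cognitive measure.** The two uses are at different visits, so that alone is not circular.

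**Conclusion.** The point holds as an inconsistency that needs correcting. One statement puts biomarkers into the definition of the prognostic outcome groups, while three others and Table 3 do not. If that statement is followed, prognostic accuracy is biased upwards by an amount the article does not allow to be computed. If the symptom-based definition is followed, there is no such bias.

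The two labelling faults are certain from the text: one term for both outcome and prediction, and a negative group named as having no ATE within a TBI-positive population. Their effect on the sample size is nil: 236/157/393/786 stand once the 157 are relabelled. The mismatch over the 60% is also certain as wording. Whether it has a numerical consequence depends on which population the cited rate describes, which cannot be seen from the article.

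**What to change.** - Define the reference outcome at 14, 30 and 90 days as observed symptom status from that visit's Table 3 instruments and their interpretation guides, assigned without access to biomarker results.
- Delete the word biomarker from the sentence before Table 3 that defines the groups with and without symptoms.
- Keep high/low risk for the algorithm's output only, and in Prognosis of ATE describe the reference classes as with or without post-concussive symptoms.
- Relabel the 157 as ATE subjects without post-concussive symptoms.
- State that the 60% is assumed among adjudicated ATE subjects. If it is instead the rate among all suspected subjects, recompute the split and the total with an explicit rate within ATE.

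The cost is wording. The instruments are already collected, and no sample-size figure changes unless the 60% turns out to belong to a different population. The change should be made before the symptom classification is applied to either cohort.

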### Algorithm Training and Testing

Data collected in this study will be used to finalize development of the BRAINBox TBI Test algorithms and to provide clinical validation of test performance. Using subjects in the training cohort, the BRAINBox diagnosis will be made by including the biomarker values, NC assessments and baseline demographics (age and sex) at the initial visit as predictors in a statistical/machine learning algorithm that estimates the ATE score. The decision threshold for ATE will be determined by identifying the ATE score that meets the diagnostic characteristic of a minimum sensitivity and specificity of 85 and 75%, respectively. To create the distributions for “ATE” and “no ATE” groups, the mean and the standard deviation of the score will be calculated on a log odds scale. For those subjects in the validation set, the final algorithm will be applied to the individual's biomarker values, neurocognitive assessments, and baseline demographics (age and sex) at the initial visit. The ATE score will be the output. If the ATE score exceeds the identified threshold, the subject will be classified as having “ATE,” otherwise, the subject will be classified as “no ATE.” A sample's log odds value will be compared to the log odds distribution of the “no ATE” subjects in the training set and a corresponding percentile will be assigned to the sample as the percentile relative to that distribution.

The performance of a prognostic ATE test will be determined by evaluating the biomarker values, neurocognitive assessments, and baseline demographics at the index visit, as predictors of 3 separate models that assign high or low risk to a subject for subsequent symptom occurrence at 14, 30, and 90 days. Symptom categories and tests performed during the study are provided in Table 3. Symptoms are evaluated as a composite at each time point, with thresholds to stratify subjects defined based on the scoring system/scale for each assessment, identifying the subject's risk for a specific symptom category at each time point. A separate statistical/machine learning algorithm will be developed for each time point that calculates the risk at the specific time after injury. In the algorithm, the definition of high or low risk for having post-concussive symptoms is defined by the decision threshold that produces the minimum sensitivity and specificity of 85 and 75%, respectively. For the validation process, the finalized algorithms will be applied to the subject's biomarker values, NC assessments, and baseline demographics (age and sex) at the index visit. If the output of the algorithm exceeds the identified decision threshold, the subject will be classified as high risk. Otherwise, the subject will be classified as low risk for post-concussive symptoms at the specified time point. The prognostic report is designed to aid the clinician in determining the subject's risk of having post-injury post-concussive symptoms at 14, 30, and 90 days.

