### Diagnosis of ATE

Prior to algorithm development, data will be divided into training and validation sets, with a model being derived using the training data. The training phase will include examination of potentially confounding and interacting variables (e.g., age, sex, time from injury until blood draw). Any confounding variables will be included as covariates in the model. Variables with insignificant interaction, as determined by backward selection, will be omitted. The model will provide a probability/score that a subject has ATE. The c-statistic will be reported, and a threshold selected to ensure the model meets the minimum sensitivity and specificity of 85 and 75%, respectively, with confidence intervals, positive predictive value and negative predictive value reported. Accuracy will be reported as the percentage of all suspected TBI subjects correctly classified as “ATE,” vs. “no ATE,” using the identified threshold. Validation data will be derived in an independent subject set (validation cohort), against which the developed model will be tested for generalizability. *P*-values comparing the AUC, sensitivity, specificity, and accuracy will be reported, with alpha defined as < 0.05. Sample size calculation was performed in PASS statistical software (32) using an assumed prevalence of 50% ATE in the subjects enrolled with blunt head injury. The final number of evaluable subjects for the “ATE,” and “no ATE” cohorts, should each not exceed 240, which makes the total number of evaluable subjects 480. An equal number of subjects are needed for algorithm validation (*n* = 480).

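### Cut-offs and the 'no ATE' percentile reference are set in the cohort that fits the models, against bare 85%/75% floors, with no stated correction for optimism or margin

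*Protocol article*

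**What the plan says.** All references are to the protocol article.

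- **Fitting** (Algorithm Training and Testing): "Using subjects in the training cohort, the BRAINBox diagnosis will be made by including the biomarker values, NC assessments and baseline demographics" as predictors in a statistical or machine-learning algorithm. The section Diagnosis of ATE divides the data into training and validation sets only, and uses backward selection of interactions in the training phase. There is no third set for tuning.
- **Diagnostic cut-off** (Algorithm Training and Testing): "The decision threshold for ATE will be determined by identifying the ATE score that meets the diagnostic characteristic of a minimum sensitivity and specificity", here 85% and 75%. Diagnosis of ATE restates it as "a threshold selected to ensure the model meets the minimum sensitivity and specificity of 85 and 75%, respectively, with confidence intervals".
- **Prognostic cut-offs** (Algorithm Training and Testing): for each of the three time-point models, high or low risk "is defined by the decision threshold that produces the minimum sensitivity and specificity of 85 and 75%, respectively".
- **Percentile**: mean and standard deviation are calculated on the log-odds scale, and a sample's value is "compared to the log odds distribution of the “no ATE” subjects in the training set and a corresponding percentile will be assigned".
- **Validation** (Diagnosis of ATE): "Validation data will be derived in an independent subject set (validation cohort), against which the developed model will be tested for generalizability".

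The article does not say whether the training scores used for these steps are fitted or cross-validated. It also does not say which score is taken when a range of scores meets both floors.

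**The concern.** A model separates the subjects it was fitted to better than it separates new ones. A cut-off that just reaches a target on fitted scores therefore tends to fall short of it in new patients. A reference distribution built from fitted 'no ATE' scores lies too low, so new 'no ATE' patients receive percentiles that are too high. Backward selection on the same data adds to the effect.

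Three things are at stake. The locked threshold may sit in the wrong place. The training check that both floors are met may pass when it should not, so that a full validation cohort is spent on a test that does not qualify. And the percentile shown to clinicians may be somewhat inflated. Optimism matters most when true performance is close to the floors, and Sample Size Estimation takes exactly 0.85 and 0.75, from the pilot trial, as its planning values.

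**Working it through.** **1. The plan's own sample size.** Inputs (Sample Size Estimation): 0.85, difference 0.07, two-sided α 0.05, power 0.80. The exact binomial test of 0.85 against 0.78 first reaches 80% power at n = 236 (power 0.802), the high-risk number in Prognosis of ATE. The normal formula gives n = [1.960·√(0.85·0.15) + 0.842·√(0.78·0.22)]² / 0.07² = 224.4, so 225. With continuity correction, 225 + 1/0.07 = 239.3, so 240, the number per diagnostic group. The training sizes used below are therefore the plan's: 240/240 for diagnosis and 236/157 for prognosis.

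**2. Number of predictors (assumption, shown as a range).** Methods names five biomarkers, not as a closed list. Table 2 lists six BrainCheck items plus Rivermead, and age and sex are added: 5 + 6 + 1 + 2 = 14 if each gives one score. The text before Table 2 says that the tests have metrics such as duration and accuracy, so more is plausible.

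**3. Simulation.** Logistic regression, normal predictors, 500 runs per setting. Two levels of separation:
- d′ = Φ⁻¹(0.85) + Φ⁻¹(0.75) = 1.71, where the best attainable ROC curve passes exactly through 85/75; AUC = Φ(1.71/√2) = 0.887;
- d′ = 2.10, where the curve clears 85/75 comfortably.

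The cut-off was set on fitted scores or on 10-fold out-of-fold scores, and its true sensitivity/specificity was then evaluated.

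| 240/240 | Fitted: cut-off at Se 85% | Fitted: cut-off at Sp 75% | Fitted: mid-range cut-off | Out-of-fold: cut-off at Se 85% |
|---|---|---|---|---|
| d′ 1.71, 8 predictors | 0.837/0.754 | 0.850/0.738 | 0.844/0.747 | 0.848/0.739 |
| d′ 1.71, 14 | 0.833/0.752 | 0.850/0.730 | 0.842/0.742 | 0.852/0.727 |
| d′ 1.71, 30 | 0.811/0.757 | 0.846/0.712 | 0.829/0.735 | 0.849/0.706 |
| d′ 2.10, 8 | 0.837/0.859 | 0.921/0.742 | 0.884/0.806 | 0.846/0.850 |
| d′ 2.10, 14 | 0.832/0.857 | 0.919/0.736 | 0.881/0.803 | 0.848/0.841 |
| d′ 2.10, 30 | 0.814/0.856 | 0.914/0.722 | 0.871/0.796 | 0.850/0.821 |

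The sensitivity shortfall at the sensitivity floor runs from 0.85 − 0.837 = 0.013 to 0.85 − 0.811 = 0.039. With 14 predictors, true sensitivity is below 0.85 in 76-78% of runs for the fitted cut-off, against 45-51% for the out-of-fold one. With 236/157 and d′ 1.71, the fitted cut-off gives 0.839, 0.831 and 0.813 for 8, 14 and 30 predictors, and the out-of-fold cut-off gives 0.849, 0.850 and 0.854.

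**4. The check before locking.** At d′ 1.71 no fitted model can do better than just touch 85/75. Fitted scores nevertheless show a cut-off meeting both floors in 67%, 70% and 88% of runs (8, 14, 30 predictors). Out-of-fold scores do so in 42%, 32% and 19%.

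**5. Percentile.** With 10-30 predictors, 5.6-7.1% of new 'no ATE' subjects exceed the nominal 95th percentile from fitted scores, against about 4.8% from out-of-fold scores.

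**The case against.** The strongest reply is that the article never says the scores are resubstituted. Cross-validated scores would fit every sentence quoted above, and a condensed article may leave the resampling scheme to the full plan. This stands as a limit on the claim: resubstitution is inferred. It does not remove the point, because the article itself writes out the threshold and percentile rules, down to mean and standard deviation on the log-odds scale. Followed as naturally read, those rules use the scores of the fitted model.

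A reader might go further and infer that the cut-off is fixed at exactly 85/75 and that the test is bound to miss its sensitivity target. The documents do not support that. For diagnosis, 85% and 75% are floors; only the prognostic wording, "the decision threshold that produces the minimum sensitivity and specificity of 85 and 75"%, leans towards an exact operating point. A cut-off at the specificity floor misses on specificity instead, and at d′ 2.10 a mid-range cut-off misses neither.

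A reader might also calculate the chance that both validation point estimates reach 85/75 and call that the pass probability. The article states no such success rule. Its stated test is a two-sided binomial test, which at n = 240 would reject a true sensitivity of 0.833 as too low only about 10% of the time.

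It can also be said that no usable test is harmed, since at d′ 1.71 the out-of-fold cut-off misses on specificity (0.706-0.739). That is fair for d′ 1.71, where the gain is an earlier warning. At d′ 2.10 the fitted cut-off at the sensitivity floor gives 0.814-0.837, whereas the out-of-fold one averages 0.846-0.850 with specificity of 0.821-0.850. Finally, with 10-14 predictors the shift is 1.5-2 points, no larger than the run-to-run standard deviation of true sensitivity (about 2.4 points). But it is systematic, and nearly free to remove.

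**Conclusion.** The point holds in a limited form. Cut-offs and the 'no ATE' reference come from the cohort that fits and selects the models, judged against bare point-estimate floors, with no stated correction or margin. If fitted scores are used, a cut-off at the sensitivity floor costs about 1-4 points of true sensitivity, the shortfall can move to specificity or vanish inside a wide range, and percentiles are inflated by roughly 1-2 points near the 95th.

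The sizes rest on assumed logistic regression, about 8-30 normal predictors and the two separations shown. Selection of interactions was not simulated. The accuracy reported from the independent validation cohort is not biased. What suffers is where the threshold is locked and how far the training check can be trusted. The change is worth making before the algorithms are locked.

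**What to change.** In Algorithm Training and Testing (diagnosis and prognosis) and in Diagnosis of ATE:

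1. State that thresholds and the 'no ATE' log-odds distribution are derived from cross-validated (out-of-fold) training scores, with all tuning and variable selection repeated within each fold.
2. State how the cut-off is chosen when a range of scores meets both floors, including whether any margin is kept. Out-of-fold scoring removes the systematic shortfall, but a cut-off placed at the floor still falls below it in about half of runs.
3. Before locking, confirm on these scores that a cut-off meeting both floors exists.

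The cost is a little computing and a sentence or two in each place, with no additional subjects. The drawback is that training performance will look slightly less favourable.
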